**Statistical analysis.** The effects of the intervention will be assessed on the intention-to-treat principal using linear mixed models for continuous variables and by a general estimation equation for categorical variables. The primary outcome is tested for group-interaction over time using an interaction contrast ( $t_{\text{time} \times \text{group}} = \mu_{\text{BL,int}} - \mu_{\text{FU,int}} - \mu_{\text{BL,cont}} + \mu_{\text{FU,cont}}$ ,  $t$ : contrast test statistic,  $\mu$ : estimated marginal mean, BL: baseline, FU: follow-up, int: PTCT intervention, cont: PT control) in a linear model for longitudinal data accounting for within-person correlation and different variances at the two time-points. Negative binomial regression will be used to estimate the incident rate ratio for falls. The Cox proportional hazard regression model will be used to calculate hazard rates for fallers in both groups with PT as a reference. In addition, individual changes in the main and secondary outcomes observed during the study will be calculated and a reliable change index computed.

**Research material, materials management plan and confidentiality of data.** A quality assurance system will be set up. This includes a written standard operation procedure as well as periodical meetings and checks for monitoring the intervention and quality of data collection. The personnel performing the measurements and supervising the interventions will be carefully educated. Data will be collected by questionnaires, interviews, health examinations and laboratory tests. Interview-based data will be collected using computer-assisted personal interviewing (SPSS Data Entry Builder software, SPSS Inc). Each participant will be assigned an identification number. The identification -key will be in the possession of the research coordinator, research nurse and PI during the data collection and thereafter in the possession

of the PI only. All information collected on paper will be locked in a cabinet at GEREK and saved as data files as soon as possible. Data files will be stored on the UJ server and protected by passwords. The research data will be owned by the UJ and managed by the PI or a person specifically appointed for this task. When participating in the project, researchers will be able to use the data for research and teaching while in the University's employ. If necessary, permission to use the data may also be granted to researchers who change their employer. The main results will be published by the research group. Data will also be available to other investigators for additional analysis, as individually agreed with the research group. Information on the study design and outcomes will be available at the ISRCTNR and in a design paper published in an open access journal.

**Research infrastructure.** *This study will be conducted at the Gerontology Research Center, Department of Health Sciences, Faculty of Sports and Health Sciences, University of Jyväskylä (UJ, GEREK, <http://www.gerec.fi/en>). The GEREK has app. 30 staff members including professors, senior researchers, lecturers, post-doctoral and doctoral students. This project has full support from the Department, the Faculty and the UJ. The UJ has set gerontology as an international leading edge strategy. In partnership with the Health and Physical Activity Laboratory of the UJ, GEREK has extensive up-to-date facilities for the assessment of physical functioning. The biochemistry laboratory of the Faculty has up-to-date methodology needed for the haematology analysis in this study.*

CIBR (<http://cibr.jyu.fi/>) provides state-of-the-art infrastructure for performing brain imaging studies, including e.g. MEG laboratory and several EEG laboratories, behavioural and psychophysical test booths, and a dedicated fire-wall protected data server with modern analysis softwares. Combined EEG/MEG recordings are possible in CIBR. CIBR offers well-structured practical training, access protocols and support personnel for designing and setting up a neuroimaging study, as well as for analysis and technical aspects.

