*Contamination of study groups:* All participants will receive the same physical training intervention and half will also receive cognitive training. PT-only group may become interested in cognitively challenging exercises. They are, however, unlikely to adapt a training regimen as intensive as that designed for this study and also organized separately. Some studies have used cross-over and cluster randomization to overcome the risk of contamination. In this study, due to the post-intervention follow-up, it is crucial that all participants remain in their original randomly assigned study group. Moreover, the effects of the physical and cognitive training may last for months which in this study would mean an over-long washout period. Cluster randomization designs are susceptible to recruitment bias and require much larger sample size than individually randomized trials.

*Adherence and drop-out rates:* Drop-out was taken into account in our sample size calculations. Adherence will be monitored and drop-outs carefully documented. The effects of the intervention will be analysed by the intention-to-treat –principle.

*Double blinding:* Double blinding is not possible. To ensure blinding of the study personnel, participants will be asked not to disclose their group allocation to the assessors or other participants.

*Personnel:* It is important that the *personnel* involved in the data collection remain unchanged in repeated measures designs. Our experience is that research assistants recruited from among University students are able to commit to long-term research projects. We will, however, have a back-up system for data collection in place in case of sickness leaves and other impediments.

*Sample size calculations:* No data on the combined effects of PT and CT were available. We were able to find reliable data on the effects of PT on walking speed, but data on the effects of CT were scanty. Only a few small-scale pilot studies on the effects of CT have been published and in those studies a large treatment effect (>10%) was observed. Due to the small amount of available data and possible publication bias related to the effects of CT on walking speed, we have halved the earlier published treatment effects for the sample size calculations (for details, see paragraph 4).

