**Sample size.** A priori sample size calculations are based on previously published and our own data on 10-m walking speed. Our own data (SCAMOB) give reason to expect a baseline mean level of 1.3 m/s (standard deviation of 0.36 m/s) in both groups. We expect the PT intervention to induce a 4 percentage point mean increase in both groups and a 6 percentage point higher mean in the PTCT group than PT group. The SD is expected to remain unchanged in both groups. The follow-up within-person correlation for the two measurements, obtained from SCAMOB, is estimated to be  $r=0.80$ , yielding 0.23 m/s as an estimate of the SD for change. Setting the significance level at 0.05 and power at 80 % for the group-time interaction favouring the PTCT vs. the PT group indicated that a sample size of 135 participants per group would be required. The power analysis was based on Diggle et al. (2002) and verified by a simulation study with Mplus-software version 7. Given an anticipated dropout level of 15 %, we decided to recruit 155 participants per group. A additional power analysis was calculated for the secondary outcome of falls rate based on recently published data and formulae in Zhu & Lakkis (2014) for negative binomial distribution outcomes (intercept: 0.56, dispersion 0.64). At 80 % power and with a total sample size of 270-310, depending on the dropout rate, it would be possible to detect a difference of 27-29 % in falls rate significant ( $\alpha=0.05$ ) between the PT and PTCT groups.

Our sample size calculations are conservative. For comparison, a recent meta-analysis reported the mean effect of multicomponent PT on walking speed to be 8%. The mean effect of CT on walking speed has been reported to be 11%. Moreover, in a recent two-year falls prevention study, a 30% difference in falls rate between the exercise and non-exercise control group was expected.

**Measurements.** *The main outcome of this study is 10-m walking speed.* Participants are asked to walk as fast as possible over the 10-m course. The time to complete the walk will be measured by photocells. Low walking speed is associated with e.g. increased risk for disability, cognitive impairment, institutionalization and falls. It has also been used to establish thresholds for community activities such as the ability to cross the street safely.

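### At the plan's own 15% dropout, 155 recruited per group leaves about 132, not the 135 it requires; the cost is about one point of power

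*Protocol*

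**What the plan says.** The calculation is in the Protocol, section 4, under Sample size.

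- **Inputs.** The authors "expect a baseline mean level of 1.3 m/s (standard deviation of 0.36 m/s) in both groups". They assume "a 6 percentage point higher mean in the PTCT group than PT group". A within-person correlation of 0.80 is given, "yielding 0.23 m/s as an estimate of the SD for change".
- **Target.** "Setting the significance level at 0.05 and power at 80 % for the group-time interaction favouring the PTCT vs. the PT group", the calculation leads to 135 participants per group.
- **Dropout.** "Given an anticipated dropout level of 15 %, we decided to recruit 155 participants per group". No inflation formula is shown.
- **Falls.** The power statement for the falls rate works "with a total sample size of 270-310, depending on the dropout rate", and reports a detectable difference of 27–29% at 80% power.

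Section 3, in the paragraph on adherence and drop-out, relies on this step: "Drop-out was taken into account in our sample size calculations". The total of 310 is also used in section 3 (Recruitment) and section 4 (Participants and recruitment).

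**The concern.** A sample size paragraph that gives a required number, a dropout rate and a recruited number makes a claim that can be checked: after the stated loss, the required number remains. Here it does not. The falls sentence shows that 135 is meant as the retained number, because its range runs from 2 × 135 = 270 to 2 × 155 = 310 and is said to depend on dropout. But going from 310 to 270 is a 12.9% loss, not 15%. The paragraph therefore states one dropout rate and uses another.

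What is at stake is the accuracy of the power claim, not the soundness of the trial. The 135 was set almost exactly at 80%, so any shortfall takes the plan's own calculation below its target. The same paragraph calls the calculations conservative, and the dropout step errs the other way. The protocol also announces a registry entry and a design paper, where such a paragraph would probably be reused.

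**Working it through.** **Inputs (Protocol, section 4, Sample size).** Baseline mean 1.3 m/s; SD 0.36 m/s; r = 0.80; difference of 6 percentage points; alpha 0.05; power 80%; 135 required, 15% dropout and 155 recruited per group. Allocation is to groups of equal size (Randomization and blinding). Sidedness is not stated. I assume two-sided, because that reproduces the plan's number.

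**Step 1: reproduce the 135.**

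- Difference: 0.06 × 1.3 = 0.078 m/s.
- SD of change: 0.36 × √(2 × (1 − 0.80)) = 0.2277 m/s, printed as 0.23.
- n per group = 2 × (1.960 + 0.842)² × SD² / 0.078². This gives 133.8, so 134, with SD 0.2277, and 136.5, so 137, with SD 0.23.
- The plan's 135 lies between the two. A one-sided test would give 106–108 and does not fit.

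**Step 2: dropout.**

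| Quantity | Arithmetic | Result |
|---|---|---|
| Left per group at 15% loss | 155 × 0.85 | 131.75 |
| Needed per group to keep 135 | 135 / 0.85 | 158.8, so 159 |
| Multiplying instead of dividing | 135 × 1.15 | 155.25 |
| Loss that 155 tolerates | 1 − 135/155 | 12.9% |
| Total left at 15% loss | 310 × 0.85 | 263.5, about 264 |

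**Step 3: effect on power.** Two-sample t-test on change, difference 0.078 m/s, noncentral t with noncentrality 0.078 / (SD × √(2/n)):

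| SD of change | n = 135 | n = 131.75 | Loss |
|---|---|---|---|
| 0.2277 (unrounded) | 80.1% | 79.1% | 1.0 point |
| 0.23 (as printed) | 79.3% | 78.3% | 1.0 point |

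Each row must be read across. Going from 80.1% to 78.3% would add the effect of rounding the SD (80.1 − 79.3 = 0.8 point) to that of dropout.

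**Step 4: falls.** The plan gives an intercept of 0.56 and a dispersion of 0.64. I assume that the intercept is on the log scale, so the control rate is λ₀ = exp(0.56), and that exposure is T = 2 years (12-month intervention plus one-year follow-up). The detectable rate ratio solves

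n × (ln RR)² = (1.960 + 0.842)² × [(1/T)(1/λ₀ + 1/(λ₀ × RR)) + 2 × 0.64], with n per group.

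| Total N | Detectable reduction |
|---|---|
| 310 | 27.0% |
| 270 | 28.7% |
| 264 | 29.0% |

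These assumptions reproduce the plan's 27–29%, and the range still holds at 264.

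**The case against.** The best case on the other side accepts the arithmetic and disputes whether it matters.

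- **The loss is tiny.** It is one point of power, and 155 is within 3% of 159 (4/159 = 2.5%). This stands, and it is why the point is minor. Rounding the SD moves power almost as much.
- **Completers-only power is pessimistic.** The plan specifies intention-to-treat with linear mixed models and a 6-month visit, so people who leave before 12 months can still contribute. This stands in part. The gain may be small, because the primary contrast is written for two time-points.
- **Dropout may be lower.** Section 3 reports less than 10% in the team's earlier studies. At 10%, 155 × 0.90 = 139.5 remain and power is 81.4% (SD 0.2277). This is reassuring about the trial, but 15% is the rate the plan chose and its printed figures should agree with it.
- **The effect can be read differently.** If the 6% applies to the mean after the 4% gain (1.3 × 1.04 = 1.352 m/s), the difference is 0.0811 m/s and power at 131.75 is 82.2% (SD 0.2277) or 81.4% (SD 0.23). This is possible, but 0.078 fits the plan's 135 better: with 0.0811 the required number would be 124–127.
- **The inflation formula is not printed.** Multiplication by 1.15 is an inference from the match. The mismatch does not depend on it.

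A reader might go further and infer that the trial is underpowered and must enrol more, or that the falls calculation is wrong. The documents support neither. A one-point change in a completers-only figure does not call for more participants, and the falls sentence does not label 270 as the number left at 15% dropout.

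**Conclusion.** The point holds as a minor inconsistency. At the stated 15% dropout, 155 per group leaves about 132, which is 3.25 per group short of 135 (6.5 in total). Keeping 135 would take 159 per group, or dropout of no more than 12.9%. Completers-only power for the change contrast is about 79% (78.3–79.1%, depending on SD rounding), one point below the value at 135 in either case.

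This rests on a two-sided test, a difference of 0.078 m/s and no information from participants who drop out. The falls conclusion is unaffected: with a log-scale intercept and two years of exposure, both assumed, the detectable difference stays within 27–29% at 264.

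**What to change.** Reword the dropout sentence in section 4 in one of two ways:

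1. 155 per group leaves about 132 per group at 15% dropout, which gives about 79% power for the change contrast on a completers-only basis; or
2. 155 per group retains the required 135 if dropout does not exceed 12.9%.

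For consistency, give the falls sample range at 15% dropout as 264–310 in place of 270–310, and leave 27–29% as it is. Stating the inflation formula would let a reader check the step.

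The cost is a few words and a power figure about one point less favourable. Enrolment, design and analysis stay as they are.

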calls will be made if necessary. After the telephone interview, examination by a nurse, and if necessary, a physician, will be arranged. *Inclusion criteria* are 1) age 70 to 85, 2) living independently in the City of Jyväskylä, 3) sedentary or only moderately physically active (less than 150 min of walking per week and no attendance at gym activities), 4) able to walk 500 m without assistance, 5) intact cognition (Mini Mental State Examination Score, MMSE  $\geq 24$ ), and 6) informed consent to participate. *Exclusion criteria* are 1) severe chronic condition or medication affecting cognitive and/or physical function (e.g. cancer, severe psychiatric disorder, 2) excessive and regular use of alcohol (more than 14 portion per week in women and 21 in men), 3) contraindication for physical exercise or walking tests.

If, for some reason, we are unable to recruit enough participants with this strategy, we will send the information letter to the remaining one third of the population that was not contacted during the initial recruitment phases.

**Randomization and blinding.** Participants will be randomized into groups of equal size after baseline measurements. A computer-generated random allocation sequence of two-fold stratification by gender and age (70-74, 75-79, 80-85) with blocks of 20 will be designed by a biostatistician blinded to the study participants. After the baseline, the research coordinator will run the randomization program to assign the participants to the study groups. Group allocation will only be known by the research coordinator, nurse and physician. Outcome assessors, but not participants, will be blinded to study group.

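### The primary group-by-time contrast subtracts a separately estimated baseline mean in each arm, which is valid but costs about 9–10% of the information under the plan's own assumptions

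*Protocol*

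**What the plan says.** The Statistical analysis paragraph of Protocol section 4 fixes the primary test by formula: "The primary outcome is tested for group-interaction over time using an interaction contrast". The contrast is baseline minus follow-up in the PTCT arm, minus baseline minus follow-up in the PT arm. Each of the four terms is an estimated marginal mean, and each arm has its own baseline term. The contrast is evaluated "in a linear model for longitudinal data accounting for within-person correlation and different variances at the two time-points". The paragraph mentions neither a baseline mean shared by the arms nor baseline walking speed as a covariate.

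The Randomization and blinding paragraph says: "Participants will be randomized into groups of equal size after baseline measurements".

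The Sample size paragraph works from the same quantity as the test. The data "give reason to expect a baseline mean level of 1.3 m/s (standard deviation of 0.36 m/s) in both groups", the assumed effect is "a 6 percentage point higher mean in the PTCT group than PT group", and "The SD is expected to remain unchanged in both groups". The correlation "is estimated to be $r=0.80$ , yielding 0.23 m/s as an estimate of the SD for change". The required size is 135 per group, raised to 155 for 15% dropout.

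**The concern.** Because allocation comes after baseline, both arms are drawn from one population with one baseline mean. Any observed baseline difference is a chance difference. The stated contrast estimates it and subtracts it in full, with weight 1. When the SDs at the two visits are equal, the weight that minimises the variance is the within-person correlation, here 0.80. Subtracting more than that adds noise to the treatment estimate.

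A longitudinal model with a common baseline mean, or an analysis of follow-up speed adjusted for baseline speed, estimates the same treatment effect from the same measurements with a smaller standard error. What is at stake is precision and power for the primary comparison. Bias and type I error are not at issue.

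**Working it through.** **Inputs** (Protocol section 4, Sample size): baseline mean 1.3 m/s; SD 0.36 m/s at both visits; r = 0.80; effect 6% of 1.3 = 0.078 m/s; alpha 0.05; power 80%; 155 recruited per arm; 15% dropout. Sidedness is not stated. I take it as two-sided, because a one-sided calculation gives only 106–108 per arm and does not match the plan.

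**1. Reproduce the plan.**
- SD of change = 0.36 × √(2 × (1 − 0.80)) = 0.2277 m/s, which the plan rounds to 0.23.
- A two-sided t-test for 0.078 m/s at 80% power needs 135 per arm, the plan's figure. The normal approximation gives 134, or 137 with the rounded SD.

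The plan was therefore sized for a comparison of change scores.

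**2. Baseline-adjusted analysis, complete data.**
- Residual SD = 0.36 × √(1 − 0.80²) = 0.216 m/s.
- Variance ratio, adjusted to change score = (1 − r²) / (2(1 − r)) = (1 + r)/2 = 0.36/0.40 = 0.90, a 10% loss.
- Size for 80% power by the same t-test: 122 per arm instead of 135 (normal approximation: 121 instead of 134).
- Power at 135 per arm: 84.0% instead of 80.1%.
- A simulation of 20,000 trials with 135 per arm gave a variance ratio of 0.895.

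**3. With the planned dropout and a mixed model.** Follow-ups per arm: 155 × 0.85 = 131.75. A likelihood-based model also uses the baselines of those who drop out. Assuming dropout unrelated to outcome, the variances of the treatment estimate are:
- separate baseline means: 2 × 0.36² × [(1 − 0.80²)/131.75 + (1 − 0.80)²/155] = 0.000775;
- common baseline mean: 2 × 0.36² × (1 − 0.80²)/131.75 = 0.000708.

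The ratio is 0.914, a loss of 8.6%. Power is about 79.7% versus 83.2%, a difference of about 3.5 points.

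**4. Sensitivity to the SD ratio.** The model allows the variance to differ between visits. With k = follow-up SD / baseline SD and complete data, the variance ratio is k²(1 − r²) / (1 + k² − 2rk). At r = 0.80:

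| k (assumed) | Variance ratio | Loss |
|---|---|---|
| 0.9 | 0.2916/0.3700 = 0.788 | 21% |
| 1.0 (the plan) | 0.3600/0.4000 = 0.900 | 10% |
| 1.1 | 0.4356/0.4500 = 0.968 | 3% |
| 1.25 | 0.5625/0.5625 = 1.000 | 0% |

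The optimal weight on the baseline difference is rk. It equals 1 at k = 1.25, so the loss vanishes there. The denominator minus the numerator is (1 − rk)², which is never negative, so in large samples adjustment is never less precise.

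**5. Sensitivity to r**, at equal SDs: the loss is 5% at 0.90, 15% at 0.70 and 20% at 0.60 (assumed values).

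**The case against.** The strongest reply is that nothing here is wrong. The contrast is a standard group-by-time test, it is unbiased under randomisation, and the trial was sized for exactly this test. That stands, and it limits the point to efficiency. A reader might infer that the primary test is invalid or that the 80% power is overstated. The documents support neither, since 135 per arm is what the change-score basis requires.

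A second reply is that separate baseline means are an inference. The fixed effects are not listed, a statistical analysis plan may add a constraint, and under a common baseline mean the two baseline terms would cancel. This is fair as a caution. But the formula carries a baseline term for each arm, no constraint is stated, and the sample size uses the SD of change, so separate means are the natural reading. The protocol has written out the estimator rather than left it open.

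A third reply concerns size. A two-sample t-test on completers (131.75 per arm) gives 79.1% for the change score, which would suggest a gain of about four points and a trial below its target. That is the wrong comparator, because the planned mixed model keeps the baselines of dropouts and gives about 79.7%. Nor should 79.7% be read as a shortfall caused by the contrast: it arises because 155 less 15% is slightly under 135. The 10% is also not a fixed figure, since it depends on the SD ratio and on r.

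Finally, a reader might infer that 6-min walking distance and dual-task cost lose more. The protocol attaches this contrast to the primary outcome only and gives no correlation for those measures, so no such size can be claimed.

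**Conclusion.** The point holds as a loss of precision in a valid and internally consistent primary analysis. Under the plan's r = 0.80 and unchanged SD, the stated contrast gives up 10% of the information with complete data, equivalent to 13 participants per arm (135 − 122). With the planned dropout and a mixed model it gives up about 9%, or roughly 3.5 points of power. These figures assume separate baseline means per arm, a two-sided test and dropout unrelated to outcome. If the follow-up SD differs from the baseline SD, the loss could range from about 21% (ratio 0.9) to none (ratio 1.25). The change is worthwhile because it costs nothing in data. Leaving the contrast as it is would not invalidate the result.

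**What to change.** In the Statistical analysis paragraph of section 4, keep the longitudinal model with within-person correlation and visit-specific variances, but constrain the two arms to a common baseline mean. Define the primary test as the PTCT–PT difference in 10-m walking speed at the follow-up visit used in the primary contrast. Adjusting follow-up speed for baseline speed is an acceptable alternative. The two are close but not identical when follow-up is incomplete, so one should be named.

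The sample size paragraph can stay as it is, and the gain then serves as a margin. Using the same model for other continuous outcomes is reasonable, without a claimed gain. The cost is one sentence of wording, with no new data and no change in conduct. It should be settled before any comparison of the arms is seen.

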**Interventions.** *The interventions, comprising individually targeted progressive supervised training sessions and home exercises, will last for 12 months. Supervised sessions will aim at the maximal training effects whereas home exercises facilitate the adaptation to active lifestyle. Intensity, resistance, difficulty and number of training sessions will be increased during the training period. Training adherence will be carefully monitored.* Supervised sessions will be organized in groups of 10-15 participants. A diary on all home exercises will be kept on a daily basis. During summertime (June-July), extra home exercises will be provided for those who are unable to attend supervised sessions. During the first month of intervention, physical training only will be organized. This arrangement will allow participants to adapt to the training on a weekly basis. The acceptability of the interventions will be assessed by a questionnaire. For the post-intervention follow-up, encouragement to continue physical and cognitive training, but no support, will be given. The interventions are summarized in **Table 1** and described in the text below.

**Table 1.** Summary of interventions.

| Intervention/Months                | 1                                | 2-4                                                    | 5-7                                                      | 8-10                                                 | 11-12                                                     |
|------------------------------------|----------------------------------|--------------------------------------------------------|----------------------------------------------------------|------------------------------------------------------|-----------------------------------------------------------|
| Physical training (PT)      |                                  |                                                        |                                                          |                                                      |                                                           |
| Supervised sessions, fr/wk         | 1                                | 2                                                      | 2                                                        | 2                                                    | 2                                                         |

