*The cognitive computer-based training (CT)* will target working memory and different components of executive functions, that are all sensitive to the aging process and are associated with walking. The CT program will be a modification from the FINGER -study. Multidomain CT activates larger neuronal networks and is more likely to elicit transfer effects than single domain training. It also enables variation in training sessions, which may increase training compliance. Computer-based exercises enable individually adjusted progression by increasing the level of difficulty. Training sessions, supervised by psychology students, will be organized in the computer class at UJ. During the first four weeks of CT, peer support for the required computer skills will be organized in collaboration with the local University of the Third Age (UTA). UTA-run Geronet-computer courses have a well-developed peer support tutor system. (<https://kesayo.jyu.fi/ikaantyvienyliopisto/en>). For the home exercises, those who lack access to a computer at home will have possibility to train in one of ten locations provided by the City of Jyväskylä. (libraries, sheltered accommodations, etc). In each location a Geronet tutor will be present each week for 2-3 hours at a time. We can also provide 10 participants with laptop computers for training at home.

*Participants in the PT group* will receive PT only and thus, they participate in 1 to 2 supervised sessions per week. *Participants in the PTCT group* will receive both training regimens. In order to facilitate participation in the supervised training sessions, supervised walking sessions will follow one of the supervised CT sessions. Consequently, the participants in the PTCT group will attend 2-4 supervised sessions per week on 1-3 different occasions.

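### The primary model and the 135 per group make no allowance for clustering by training group, although cognitive training groups exist only in PTCT; any correlation within them would make the standard error too small and the 80% power too high

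*Protocol*

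**What the plan says.** Section 4 (Randomization and blinding) randomises individuals to two equal groups. Section 4 (Interventions) then describes a 12-month programme and states: "Supervised sessions will be organized in groups of 10-15 participants". All participants receive the physical training and half also receive the cognitive training (Section 3, Contamination of study groups). CT is supervised by psychology students in a university computer class, once or twice a week from month 2 (Table 1). For PTCT participants, "supervised walking sessions will follow one of the supervised CT sessions".

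Section 4 (Statistical analysis) tests a group-by-time contrast "in a linear model for longitudinal data accounting for within-person correlation and different variances at the two time-points". No term for training group or instructor is mentioned.

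Section 4 (Sample size) assumes "a baseline mean level of 1.3 m/s (standard deviation of 0.36 m/s) in both groups", "a 6 percentage point higher mean in the PTCT group than PT group" and a within-person correlation of 0.80, and "indicated that a sample size of 135 participants per group would be required". It contains no ICC or design effect. Clustering appears only where cluster randomisation is considered as a remedy for contamination and set aside: "Cluster randomization designs are susceptible to recruitment bias and require much larger sample size than individually randomized trials".

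**The concern.** Individual randomisation makes participants independent at allocation, but group delivery can make their outcomes dependent afterwards. People who train together for most of a year share supervisors, pace and attendance climate, so their changes in walking speed may be correlated.

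Because CT groups sit entirely within PTCT, any variance between them enters the PTCT mean and so the PTCT versus PT difference. A model that allows only for correlation within a person leaves that variance out of the standard error. The confidence interval would then be too narrow, the test would reject a true null more often than 5%, and a test that accounts for groups would have less than 80% power. The 6-min walk and the dual-task cost would be affected in the same way.

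**Working it through.** **Inputs from Section 4, Sample size.** Baseline mean 1.3 m/s, SD 0.36 m/s, within-person correlation 0.80, between-group difference 6 percentage points, alpha 0.05, power 80%. Group size m = 10 to 15 comes from Section 4, Interventions. **Assumed, because the Protocol gives none:** ICC of the change score 0.01, 0.02 or 0.05, with one stable group per participant.

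**1. The Protocol's own figure.**
- SD of change = 0.36 × √(2 × (1 − 0.80)) = 0.2277, stated as 0.23.
- Difference = 0.06 × 1.3 = 0.078 m/s.
- n = 2 × (1.96 + 0.84)² × 0.2277² / 0.078² = 134 per group; 135 with the t distribution.

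The 135 therefore reproduces with a two-sided test and independent participants (one-sided gives 106). It leaves no room for a design effect above 1.

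**2. Formulas with clustering, 135 analysed per arm.**
- Design effect DE = 1 + (m − 1) × ICC.
- Standard error under independence: SE₀ = 0.2277 × √(2/135) = 0.0277.
- Clustering in PTCT only: SE = 0.2277 × √((DE + 1)/135).
- Clustering in both arms, with arm-specific groups: SE = 0.2277 × √(2 × DE/135).
- Power with the correct SE = Φ(0.078/SE − 1.96).
- False-positive rate of the planned test = 2 × (1 − Φ(1.96 × SE₀/SE)).

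**3. Worked example, PTCT only, m = 12, ICC 0.05.** DE = 1 + 11 × 0.05 = 1.55. SE = 0.2277 × √(2.55/135) = 0.0313. Power = Φ(2.49 − 1.96) = 70.3%. False-positive rate = 2 × (1 − Φ(1.736)) = 8.3%.

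**4. Results for groups of 10 to 15 (normal approximation).**

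| Clustering | ICC | SE increase | Power | False-positive rate |
|---|---|---|---|---|
| none | 0 | 0 | 80.4% | 5% |
| PTCT only | 0.01 | 2.2-3.4% | 78.6-77.7% | 5.52-5.81% |
| PTCT only | 0.02 | 4.4-6.8% | 76.9-75.1% | 6.05-6.64% |
| PTCT only | 0.05 | 10.7-16.2% | 72.0-67.8% | 7.66-9.16% |
| both arms | 0.01 | 4.4-6.8% | 76.9-75.1% | 6.05-6.64% |
| both arms | 0.02 | 8.6-13.1% | 73.6-70.1% | 7.12-8.32% |
| both arms | 0.05 | 20.4-30.4% | 64.7-57.9% | 10.36-13.28% |

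**5. Small-sample check.** A simulation of change scores (20,000 runs, 135 per arm, m = 12, ICC 0.05) gave the unadjusted test a false-positive rate of 8.3% (PTCT only) or 10.8% (both arms). A test on group means with Satterthwaite degrees of freedom held 5.0% or 4.8%, with power 68.0% or 58.9%. The normal approximation gives 70.3% and 61.8%, so limited degrees of freedom cost about 2 to 3 further points.

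**The case against.** **The effect is conditional.** It needs a positive ICC and reasonably stable groups, and the Protocol documents neither. Sessions per week change by phase, some participants replace June-July sessions with home exercise, and one person may belong to different CT, walking and gym groups. Supervised CT lasts 10 to 20 minutes, once or twice a week, with individually adjusted difficulty and further training at home. The outcome is timed by photocells with blinded assessors. All this may keep the ICC low, and at 0.01 in PTCT only the loss is about 2 to 3 points. This stands. A reader might infer that the standard error is too small as a matter of fact; the document supports that only if outcomes correlate within groups.

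**Physical training groups may mix the arms.** Participants are asked not to reveal their allocation to other participants, which makes most sense if the arms meet, and only the cognitive regimen is described as organised separately. Placing PTCT walking sessions after CT is scheduling; it suggests arm-linked walking groups but does not establish them. If sessions are mixed, the shared effect largely cancels in the contrast. This also stands. A reader might take the both-arms figures as the expected loss, but the Protocol does not state the arm-specific groups they need.

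**The random-effects structure could be left to the SAP.** A linear mixed model can take a group term, and a SAP that is not shown might add one. This does not remove the point. The Protocol names the dependence its primary test handles and sizes the trial on independence; a later model term would not restore the stated power.

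**The remark on cluster randomisation concerns contamination.** That is correct, and it should not be read as a position on group delivery. Nor does the point rest on season, which the Protocol says the design controls for.

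**Conclusion.** The point holds in conditional form. CT groups are nested in PTCT by design, and neither the stated primary model nor the sample size allows for them. For any positive ICC in those groups the direction is clear: the planned standard error is too small and the 80% power too high.

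The size depends on an ICC that the Protocol does not give. The one-arm rows of the table are the ones the document supports. They run from a minor loss at ICC 0.01 to roughly 8 to 13 points of power at ICC 0.05, where the planned test's false-positive rate is about 8-9%. The both-arms rows apply only if physical training groups turn out to be arm-specific. The figures assume one stable group per participant and 135 analysed per arm. At ICC zero nothing is lost.

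**What to change.** 1. Record each participant's training group (wave, CT and walking group, and gym group), and state whether physical training groups are arm-specific and whether membership is fixed.
2. Add to the primary linear mixed model a random training-group effect on the change component. Place it in PTCT only (partially nested), or in both arms if physical training groups are arm-specific. Use Satterthwaite or Kenward-Roger degrees of freedom. Do the same for the 6-min walk and the dual-task cost.
3. In Section 4, Sample size, state that 80% power assumes no training-group clustering, and give power over ICC 0.01 to 0.05. At groups of 12 (normal approximation) this is about 78% to 70% with clustering in PTCT only, and about 76% to 62% with clustering in both arms; small-sample degrees of freedom lower it a little further.

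The cost is one variable already known from session scheduling, one model term, slightly wider intervals, fewer degrees of freedom and a less favourable stated power. If the true ICC is zero, a group-mean analysis loses about 1 to 5 power points, and a mixed model would typically lose less. No change in enrolment is proposed, so 80% power is not restored if the ICC is above zero. For scale, restoring it at ICC 0.05 with clustering in PTCT only would take (DE + 1) × (0.2277 × 2.80/0.078)², which is 164 to 181 analysed per arm for groups of 10 to 15.
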